#### 2.3.6. Survey data analysis

Survey data analysis will be conducted at mid- and endpoints of the data gathering phase. The mid-point analysis will enable further recruitment where a sample is insufficient and to produce indicative results to inform analysis.

Logistic regression will be used to test the study’s null hypothesis, that there is no significant difference in victimisation by the jurisdiction. In addition, we will assess whether action and harm are mediated by socio-demographic category (gender, ethnicity, age, sexual orientation, citizenship status, income/financial autonomy). Other variables included in the survey are: attitudes to policing, criminal justice response and access to support. Information on conditional consent specific to sex work will also be analysed–for example, under-payment/non-payment, condom removal (‘stealthing’)–as will situations in which consent could not be given; because of intoxication, for example.

Multivariate analysis will be used to identify clusters of respondents by experience of victimisation, jurisdiction and sex work sector with the aim of producing the first statistical international typology of respondent experiences of sexual violence (and justice/support after it) in sex work. Whilst our preference is to use either AHC (Agglomerative Hierarchal Clustering) or PCA (Principal Components Analysis) to generate the clusters, it is unlikely that all variables can be converted into numerical form. Should this not be possible, then our intention is to use Multiple Correspondence Analysis (MCA), which is capable of handling categorical variables. Once our clusters have been generated, we will then explore how they differ in terms of socio-demographic category (gender, ethnicity, age, sexual orientation, citizenship status and income) in different jurisdictions and sex work sectors.

Statistical analysis, reports and publications will be, wherever possible, in line with the SAMPL guidelines [41].

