### 2.3 Data collection

This is a mixed methods (quantitative and qualitative) research study, comprising three work packages:

Work Package 1: An online survey of sex workers (n = 1,000) will gather data on experiences of sexual violence in sex work across the research sites. It will analyse harms, reporting, consent, non-payment, condom removal, experience of police and support services and be analysed according to socio-demographic of respondent and sex work sectors. This will be used to answer Research Questions 1, 3, 5, 8, 10 and 13. Recruitment will be through key online sex work platforms and NGO/health outreach and support services for sex workers.

Work Package 2: Interviews with victim-survivors of sexual violence in sex work (n = 10 per research site), practitioners from NGOs and health providers, police, lawyers and prosecutors (n = 10 per research site) will explore reporting, signposting, investigation, trauma management and criminal justice system experiences. The interview sample sizes aim to reach thematic saturation at 10 practitioners (including criminal justice professionals) and 10 sex workers each of the four sites. As a minimum, 6 interviews from each group in each site should provide an 80% saturation of themes at ≤5% new information [24]. These interviews will be used to answer Research Questions 2, 4, 6 and 12. Recruitment will be through Advisory Group members and partner organisations. Peer researchers with a lived experience of sex work / sexual violence will be trained to conduct interviews with sex workers.

Work Package 3: A desk analysis of legal norms and relevant case law will assist us to understand how the legal system operates in different jurisdictions and explore how consent, violence and sex work are operationalised in legal judgements. This analysis will be used to answer Research Questions 7, 9 and 11.

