#### 2.3.2 Survey design

The online survey for this study has been iteratively through 11 drafts, developed from existing instruments, adapted for relevance to sex working populations in the study sites, with pilot elements added.

The initial draft consulted existing surveys from Survivors UK, West Cork Health Authority, The NI Department of Justice, Criminalisation of Paying for Sex Survey [25], Beyond the Gaze Online Sex Work Survey [26] and the Evaluation of Protection From Abuse (Sc) Act 2001 survey [27]. Each draft was reviewed by the research team, with three drafts written in consultation with Expert Advisory Boards in each site and an Academic Advisory Group. The consulting statistician reviewed two drafts.

The final survey utilises adapted existing victimisation survey items from the Crime Survey of England & Wales Self Completion Module: Domestic Abuse, Sexual Victimisation and

Stalking Module [28], with methodological adaptations from Walby & Towers [29] and the National Intimate Partner and Sexual Violence Survey [30]. In addition, questions for sex workers were adapted from the context of sex workers’ condom use study [31], to begin to elucidate consciousness of sexual consent.

Novel and exploratory questionnaire items were added to be relevant to sex-working populations in the study sites and to reflect the particularity of the legal context in each area. Some questions from the Beyond the Gaze [32,33] project and in Northern Ireland [34] were added. Site specific scales for different jurisdictions (comprising no more than 20% difference between surveys) were added, for example to align ethnicity and income categories with national data in the sites. Income demographics were harmonised across the sites using OECD methodology [35], and all categories were taken from 2019 existing instruments, to assist comparability across the sites.

The survey was piloted with members of Advisory Boards, sex workers and other NGOs, using test-retest methodology [36]. This was conducted to check that the questions–and their translations–accurately collect the data required, to improve the reliability of the survey instrument and minimise measurement error.

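### Jurisdiction and sector are named among the variables that form the clusters, so the typology can separate by jurisdiction even when experiences do not differ; the logistic regression test is unaffected

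*Protocol article*

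**What the plan says.** All the relevant analysis text is in section 2.3.6 (Survey data analysis) of the protocol article.

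- **Forming the clusters:** "Multivariate analysis will be used to identify clusters of respondents by experience of victimisation, jurisdiction and sex work sector".
- **Purpose:** "with the aim of producing the first statistical international typology of respondent experiences of sexual violence", extended in a parenthesis to justice and support afterwards.
- **Method:** AHC or PCA is preferred. If the variables cannot all be made numerical, which the authors expect, "then our intention is to use Multiple Correspondence Analysis (MCA), which is capable of handling categorical variables".
- **Follow-up:** "Once our clusters have been generated, we will then explore how they differ in terms of socio-demographic category". The list covers gender, ethnicity, age and sexual orientation, and the sentence ends "citizenship status and income) in different jurisdictions and sex work sectors".
- **Test of the study hypothesis, stated separately:** "Logistic regression will be used to test the study’s null hypothesis, that there is no significant difference in victimisation by the jurisdiction".

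**The concern.** Jurisdiction is the study's explanatory variable, not an experience of violence. If it is an active input to the clustering, respondents from one site are drawn together because they share a site label, whatever happened to them. Sector works the same way. Both then return as the settings in which the finished clusters are explored. A reader shown clusters that line up with legal models would take this as a finding, when part or all of it could have been put there by the choice of inputs.

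At stake is the reading of the typology, which the article presents as a first of its kind and which would sit beside recommendations on legal improvements.

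A smaller point lies in the same paragraph. PCA and MCA are described as ways to generate clusters. They give coordinates. A clustering step such as AHC still has to be applied to those coordinates, and the route the authors think most likely (MCA) is given none.

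**Working it through.** The plan gives no figure for the cluster analysis, so there is nothing to reproduce. The check is a simulation under a null in which victimisation is unrelated to jurisdiction and sector.

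**Inputs from the article.** The survey size is 1,000 (section 2.3: "An online survey of sex workers (n = 1,000) will gather data on experiences of sexual violence in sex work across the research sites"). There are four jurisdictions. The inputs are victimisation, jurisdiction and sector, and MCA is the stated method for categorical variables.

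**Assumptions, not in the article.**
- Three sectors, and one three-level demographic unrelated to everything else.
- Six or twelve binary victimisation items driven by one latent factor.
- MCA with five axes, then Ward AHC cut at four clusters.
- 100 runs per setting.

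**Why the labels carry weight.** In MCA a variable with K categories takes a share (K − 1)/Σ(K − 1) of the total inertia.
- Six binary items: Σ(K − 1) = 6 + 3 + 2 = 11. Jurisdiction takes 3/11 = 27% and sector 2/11 = 18%.
- Twelve binary items: Σ(K − 1) = 12 + 3 + 2 = 17. Jurisdiction takes 3/17 = 18% and sector 2/17 = 12%.

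Jurisdiction outweighs sector in both cases.

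**Test.** Chi-squared of cluster by each variable at 5%, with V = √[χ² / (n × (min(rows, columns) − 1))].

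Share of null runs rejecting, with median V:

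| Items | Jurisdiction and sector | Jurisdiction | Sector | Unrelated demographic |
|---|---|---|---|---|
| 6 | active | 100%, 0.685 | 51%, 0.081 | 2%, 0.049 |
| 6 | passive | 6%, 0.051 | 7%, 0.053 | 7%, 0.053 |
| 12 | active | 100%, 0.650 | 68%, 0.101 | 7%, 0.053 |
| 12 | passive | 7%, 0.052 | 6%, 0.051 | 3%, 0.051 |

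For scale, four clusters by four jurisdictions gives (4 − 1)(4 − 1) = 9 degrees of freedom, so χ² should average 9 under independence. V = 0.685 corresponds to χ² = 1,000 × 3 × 0.685² ≈ 1,408. V = 0.051 corresponds to 1,000 × 3 × 0.051² ≈ 7.8.

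The standard error of a 5% rate over 100 runs is √(0.05 × 0.95/100) = 2.2 points, so the passive rates are compatible with 5%.

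**Wider settings** (6 or 12 items; 3, 4 or 6 clusters):
- *Jurisdiction, active:* 100% of runs, V 0.55 to 0.80. A repeat with 60 runs per setting gave 97% to 100%.
- *Jurisdiction, passive:* mostly 2% to 8%, with one setting at 18%. The repeat gave 3% to 10%.
- *Sector, active:* 30% to 98% of runs.
- *A demographic tied to site* (prevalence 10%, 20%, 30% and 40% across the four sites, assumed; no link to victimisation within site): 52% to 100% of runs when active, 0% to 8% when passive.

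**The case against.** **The follow-up lists socio-demographics, not jurisdiction.** This is correct. Jurisdictions and sectors are the settings of that comparison, and no cluster-by-jurisdiction test is specified. For a demographic unrelated to site, the listed comparison is not inflated (2% and 7% of runs). Inflation arises where the characteristic varies by site. If the authors mean to compare separately within each jurisdiction, that link drops out too. The sentence does not say which is meant, and clusters made largely of one site would leave little to compare within sites.

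**The word ‘by’ is open.** It could mean clusters formed within, or described by, jurisdiction and sector. That is possible, but listing them on a par with victimisation makes inputs the natural reading, and the text permits the circular analysis.

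**The site-specific questions.** A reader might infer that site also enters through the tailored items, "comprising no more than 20% difference between surveys" (section 2.3.2). The documents do not support this. The examples are ethnicity and income categories, which belong to the comparison made after clustering. Income was also harmonised across sites. Nothing says that tailored items enter the clustering.

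**Sector labels.** A reader might infer that the typology merely recovers sector. In the base simulation V for sector was only 0.08 to 0.10, so that is too strong.

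**PCA and MCA.** AHC is named in the same sentence, and a condensed article may leave the sequence of steps to a fuller plan. The point is minor, but easily settled while the paragraph is being edited.

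**Conclusion.** The concern holds on the natural reading of section 2.3.6. With jurisdiction and sector as active inputs, clusters can separate by jurisdiction when experiences do not differ. Under the assumed MCA and Ward settings this happened in essentially every null run, with V about 0.55 to 0.80, against about 5% in most settings when both were passive. The size depends on how variables are weighted, the axes kept and the number of clusters, none of which the article fixes. The effect on sector is weaker and varies with the settings. Socio-demographic contrasts are affected only where the characteristic is tied to site.

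A typology formed this way could not support statements that types of experience differ by legal setting. A reader might go further and conclude that the study's jurisdiction finding is an artefact. The documents do not support that: the null hypothesis is tested by logistic regression, separately from the clusters, and could still show a real difference in victimisation. The harm is limited to the exploratory typology. The wording should be corrected before analysis, but this is not a flaw in the main inference.

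**What to change.** Reword the clustering paragraph of section 2.3.6 as follows.

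1. Form clusters only from victimisation, reporting and justice or support items that are the same in all four surveys.
2. Enter jurisdiction, sector and socio-demographics as supplementary (passive) variables, and compare the finished clusters on them afterwards.
3. State that PCA or MCA supplies coordinates and that AHC is applied to the retained ones.

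In the base simulation, leaving jurisdiction and sector out of cluster formation brought cluster-by-jurisdiction rejection from 100% of null runs to 6% or 7%.

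If the authors do want jurisdiction and sector as inputs, the paragraph should say that the typology is descriptive and that no conclusion about legal setting will be drawn from it.

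The cost is analysis wording. No new data are needed, and any site-specific items are left out of the clustering.

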#### 2.3.7. Research interviews

Semi-structured interviews will be conducted to understand why patterns occur in the different research sites, provide best practice recommendations and inform work to address barriers to support and justice for victim-survivors. Interviews will be adapted to the requirements of each site, to have regard for relevant legal, policy and practice differences. Interviewees will be given the opportunity to have the interview schedules in advance if requested.

Research team members will conduct interviews (n = 10 per research site) with NGO and health service practitioners, police and criminal justice personnel who have experience of dealing with sexual assault against sex workers. These interviews will assess practice and issues such as reporting, signposting, available resources, therapy, and criminal justice support.

Current and former sex workers–individuals who have exchanged sex for money or something of value, of any gender, ethnicity and who are over 18 years old–and who have experienced sexual violence will be interviewed (n = 10 per research site). A variety of sex work locations (brothels, on-street, online, etc.) will be included in each jurisdiction.

These trauma-informed interviews will be conducted by four trained peer researchers who are sex workers / survivors of sexual violence. Support and advice signposts will be provided to all participants. Sex worker interviewees will be recompensed for their time with shopping vouchers to the value of £50, and peer researchers are recruited, paid and contracted in accordance with best practice guidance for participation [42].

#### 2.3.8. Researcher training

The project has recruited peer ‘Experts by Experience’ researchers in each research site who have a lived experience of sex work and/or sexual violence. This peer researcher method is utilised to democratise and improve the relevance of the research process in academia [43].

A Training Needs Analysis was conducted to ascertain gaps, qualifications and experience in the team. We then devised training and learning activities to address these. It is recommended [44] that interviewers should be specially trained in violence research, because they tend to elicit more reliable responses from respondents as opposed to those who do not receive the specialised training. An Action Learning Set method was chosen to deliver this training. An Action Learning Set is a small group of people who work together to understand and improve a situation, practices and the world; all participants learn and create knowledge through the process [45]. Each participant is an equal, focussing on their own perspective of one area of the project at a time. The whole group listens, observes and reflects, and the group decides ways of progressing with it. This method ensures we have a safe space for discussion; and everyone learns from each other, with one issue worked on at a time.

The whole research team, including peer researchers, are trained together using Action and Learning Set methods, to:

Discuss the themes of the research (consent legal norms, sexual violence, sex work regulation, reporting and justice);Analyse the risks to researcher and participant when interviewing about sex work and sexual violence;Learn techniques to mitigate and manage those risks;Understand trauma-informed ways of working to protect the researcher and participant from experiencing distress;Build research interviewing skills (accessibility, active listening and communication skills, prompting, disclosure, identifying barriers to participation);Explore the ethical hurdles in researching vulnerable groups;Consider the impact of results, dissemination and engagement.

The peer researchers will be conducting interviews with survivors of sexual violence who have sex-worked or are sex working and will be involved in disseminating the survey, supported by the research team, with debriefing and reflective elements to ensure safety of participants and peers in dealing with sensitive subjects.

The team intends to apply for additional funding to include the peers in writing up and dissemination of the results, to influence policy, practice and public attitudes to sexual violence and sex work, in the future.

To ensure the integrity of this involvement, the project has adopted the 4PI National Involvement Standards [46] and the Survivors of Abuse Manifesto.

#### 2.3.9. Thematic analysis

All interviews will be anonymised and stored with a unique participant ID number, in a secure Sharepoint data store at the University of Strathclyde. They will be transcribed by professional transcribers who are contracted to the project, with Confidentiality Agreements in place.

Analysis will then be conducted within a framework process adapted from Gale [47], as follows:

Transcriptions will be coded in NVivo by one research team member for consistency.Coding will be conducted using a deductive, pre-defined coding frame (including micro, meso and macro levels of analysis), devised from the research questions and key words for the study.One sex worker and one practitioner transcript from each site will be coded inductively, to test and adapt the codebook.Emergent additions will then be indexed and reviewed. Reports by global and sub-themes, with parent and child code reports, will be accompanied by thematic network diagrams, as recommended by Attride-Stirling [48] and distributed to relevant project team members in each site for analysis and study reporting.Additional matrices and reports by themes and research questions will be produced in NVivo to highlight patterns in data, main arguments, gaps and patterns of evidence [49].

## 3. Ethics and safety

### 3.1. Ethics approvals

Approval has been granted for this study by the following Ethics Committees:

University of Strathclyde Approval: UEC20/74University of Leicester Approval: 28758-tlms1-ss/cr:criminology (03/02/2021)Queen’s University Belfast: School of Law, Research Ethics Committee (26/02/2021)University of Otago Approval: 21/007 (01/02/2021)The Commissioner of New Zealand Police–Approval signed by the Director of Evidence Based Policing (n.d.)University of Nevada, Las Vegas (UNLV) Social/Behavioral IRB: 1701767–3 (12/03/2021)

A Research Request Application was also made to the Crown Prosecution Service of England & Wales, based on the UK Government Social Research Ethics Guidance (currently pending).

#### 3.1.1. Safety and risk mitigation

Sex work is a stigmatised occupation and, as a result, many sex workers do not disclose their work. In addition, some of them are working in a criminalised context. Confidentiality, privacy and anonymity are therefore of utmost importance. This research will examine the experiences of sexual violence in sex-working populations, ¬ an issue which is sensitive and carries risk of emotional harm for everyone involved. We discuss these ethical issues below and steps we will take to mitigate the risks.

The danger of failing to hear sex worker voices accurately

This ethical dimension relates to the use and interpretation of data. There is a very real risk in research about sex work that inaccurate or misleading claims are made about a vulnerable population, which either do not seek their views or misrepresent what they say. Consequently, the overall methodological framework gives weight to the views and experiences of sex workers rather than privileging the views of other organisations such as the police and those in authority who claim to speak on behalf of sex workers. The research will adhere closely to the guidelines suggested by Jeffreys [50], as adopted by the UK Network of Sex Work Projects (UKNSWP) in 2015, which advocates for ethical, interdisciplinary scholarship which can inform grassroots activities with sex workers in communities that promote their human rights.

There are additional issues regarding ethics that are immediately evident in this project:

Potential vulnerability of participants

Sex workers are vulnerable to stigmatisation and exploitation. The normal concerns of confidentiality, anonymity and personal safety are crucial in this research, especially in ESW where sex work is partially criminalised; in Nevada where sex workers are only legal if they are working in a licensed brothel; and in Northern Ireland, where clients and other third parties are criminalised.

These sensitivities are exacerbated when we involve, as we intend to, potentially vulnerable participants who have direct and personal experiences of the matters we seek to learn about. These risks will be mitigated by the experience of the team and safeguards built into the research design as outlined below.

People who have experienced sexual violence are potentially vulnerable to emotional distress when recalling their experience in an interview. This research focuses on policy and sex workers’ experiences of law and reform, where there is less risk of causing emotional distress. We are less interested in the experience of sexual violence but rather in the processes whereby these crimes are dealt with or not, for example, individuals’ feelings about what they did to contact authorities, seek justice, seek assistance and support, or whether they felt able to do any of these things and, if not, what inhibited them from doing so.

Several steps will be taken to mitigate risk of emotional harm, physical harm, breach of confidentiality, and increasing vulnerability to exploitation:

Advisory Boards of experts, who have significant knowledge of working with sensitive groups and sensitive issues like sexual violence, provide oversight and advice to the research team.We will engage with groups representing sex workers, e. g. campaigners, activists and NGOs, who will participate in the development of interview and survey questions.Researchers will be employed and will receive training from the PI, RF and Co-Is on interviewing, methodological techniques, safeguarding and confidentiality.The researchers will be experienced in dealing with sensitive questioning and any fallout from discussing such issues.We will ensure that we do not interview anyone with obvious vulnerabilities, e. g. someone who is unable to give informed consent if they are under the influence of drugs or someone who is in extreme distress. Whilst there may be trains of practice which consider this exclusionary, the safety (in all aspects) of our participants is key.All participants recruited will be over the age of 18.Participants will be reminded of their right to terminate the interview at any time. If they do become upset, interviews will be stopped and only resumed with consent.Appropriate support will be provided where it is deemed appropriate. We will also calibrate how the participant is feeling and act accordingly regarding the timing and pacing of questions.We are aware that we cannot elicit information about ongoing police or legal cases since to do so could prejudice an ongoing case. We will be including in the consent documentation for both the survey and the interviews a warning to NOT discuss explicitly any current cases, names, etc, as this would then risk the information being requested by a court and could be construed as evidence. We will inform participants of this at the beginning of the interview and this information, as well as the participant’s response, will be recorded.Contact with support agencies is vital for the mitigation of harm to participants. Local drug charities, sex worker organisations and sexual violence advisory services are identified in each study site and contact information provided to participants.Anonymity: the survey will be anonymous.

Dealing with underage sex workers

If we become aware that we have been contacted by an underage sex worker (defined as someone of an age where special protection is given by law due to young age against sexual exploitation) then we will adhere to the longstanding convention that the researcher has a responsibility to act around issues of child protection, in line with the Economic and Social Research Council (ESRC) ethical guidelines [51]. In this case we shall directly notify a support organisation and, if necessary, the police, under the laws of each country. Likewise, if we are informed during the course of the interview about confirmed or suspected instances of trafficking for sexual exploitation, we will pass this information on for further investigation. These will be the only instances where we will make aspects of our data available to law enforcement agencies given the issues around trust.

Researcher safety in home country sites

This project involves fieldwork across a number of international sites: New Zealand, the US (Nevada), ESW, and Northern Ireland. In order to ensure the researchers’ and participants’ safety, which is paramount, a number of precautions will be taken:

Experienced RAs will be recruited for each site and supervised by the Co-I in each country.Fieldwork will only take place online or in well-lit areas that can be accessed safely by both the researcher and participants (i.e., university/support service offices).To protect researchers conducting fieldwork, they will check in with a PI or Co-I in each site before and after each interview, with emergency interview details that can be accessed by the PI / Co-I if the researcher goes out of contact.Each university’s protocols for ‘Working in Isolation/Lone Working’ and ‘Working away from the University’ will be adhered to by members of the research team during fieldwork and data collection.Recording equipment will be insured and will be carried in a discreet and secure bag. This equipment will not unnecessarily be taken anywhere in order to minimise risks.The PI, Co-Is and RAs in all countries will have monthly meetings via Skype/Zoom prior to and while fieldwork is underway. Each country’s lead researcher will meet weekly with the local RA during their contracted period.During fieldwork the RAs will not only be supervised directly by Co-Is in the team but will also be connected to established researchers and/or centres of excellence to ensure they are not isolated and can benefit from academic contacts, expertise and support.All of our research personnel, employed by the University of Strathclyde, will be covered by the University of Strathclyde’s insurance provisions whilst working overseas.Any Serious Adverse Incidents or harms are not expected, but should they occur, they will be reported to the relevant site Ethics Committee in line with granted approval conditions.

